## 2 Methods and analysis

### 2.1 Study participants and sample size

The baseline assessment for this study will be conducted at approximately 12 weeks of gestation. Follow-up visits are scheduled at approximately 20, 28, and 36 weeks of gestation, as well as at 3 months postpartum (24–32 weeks post-delivery). Figure 1 presents the detailed flowchart of this study.

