In China, patients with obesity and chronic diseases face severe challenges. Internationally, interventions for patients with obesity and chronic diseases are often supported by professional medical teams and community health programs. In contrast, Chinese patients tend to rely on hospitals and themselves. In view of China, therapeutic lifestyle intervention combined with AI technology, as an innovative intervention, is easy to implement and cost-effective. Through AI technology, personalized lifestyle advice can be provided, monitoring patient health data and timely adjusting treatment options. This intervention not only facilitates patients to receive management at home, but also can deliver professional support to meet the needs of patients in the process of lifestyle change effectively and efficiently. Therefore, research targeting this area has important practical significance and urgency.

This study designed a randomized controlled study to propose an AI-driven therapeutic lifestyle change (AI-TLC) intervention. Through personalization, continuous tracking feedback, intelligent decision aid, evaluate the influence of AI-TLC intervention on health behavior and health outcomes of obese pregnant women, determine the applicability and universality of AI-TLC intervention, provide innovative, efficient, and personalized health intervention for obese pregnant women, and provide new perspectives and methods for related scientific research and clinical practice.

Specific objectives are:

Primary: Can the intervention program driven by artificial intelligence (AI)–facilitated therapeutic lifestyle changes effectively promote improvements in health behaviors and health outcomes among pregnant women who are overweight or obese?

Sub-question 1:

Do the effects of the intervention differ among pregnant women of varying ages and degrees of obesity?

Sub-question 2: From a cost-benefit perspective, which level of intervention is the most effective (human-only vs. AI-only vs. human + AI)?

Sub-question 3: What are the short-term, medium-term, and long-term effects of this intervention program? What mechanisms need to be added to achieve better long-term outcomes?

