### 2.5 Questionnaires

Health behaviors and disease prevention interventions in obesity pregnant women will be assessed using a general information questionnaire and specific scales, and mental health status will be measured by 7-item generalized anxiety disorder (GAD-7) (27), and the Self-Efficacy Scale, which reflect participants' anxiety, self-rated status, and stress levels over the past 2 weeks. Sleep quality will be assessed using the Pittsburgh sleep quality index (PSQI), including sleep quality, time to fall asleep, sleep duration, sleep efficiency, sleep disorders, hypnotic drugs, and daytime dysfunction. The level of physical activity will be assessed using the Physical Activity Rating Scale-3 (PARS-3). This scale evaluates the intensity, duration, and frequency of physical activity over the past month. The Family Health Scale short-form (FHS-SF) will be used to measure the social and family support component, which has high reliability and validity (28). The physical and mental health status of the obese comorbidity population will be based on the five-level five-dimensional health scale, and the World Health Organization's five physical and mental health indicators (WHO-5). The health status is judged by five dimensions: mobility, self-care, daily activities (such as work, study, housework, family or leisure activities), pain or discomfort, anxiety or depression, so as to propose targeted solutions to obesity-related factors. Health literacy will be assessed using Healthy Lifestyle Scale-Short Form 4 (HLS-SF4) that evaluates the ability to access, understand, and apply health-related information. Perceived stress will be measured using the Perceived Stress Scale (PSS), which assesses the frequency of feelings and thoughts related to stress over the past month. Social support will be evaluated using Perceived Social Support Scale that measures the perceived availability of emotional and practical support from family, friends, and significant others. The scale assesses the extent to which individuals feel cared for and supported in their personal and social lives (Table 1).

**Table 1 T1:** Variables and measures collected at evaluation time points.

**Variables**		**Data source**	**Measures**	**Follow-up time point**					
				**T-0**	**T-1**	**T-2**	**T-3**	**T-4**	**T-5**
Covariates	Individual	Survey	Age, marital status, education level, occupation, annual income, ethnicity	√					

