### 2.6 Statistical analysis

Participants' socio-demographics are presented as count and proportion, and the χ^2^ test was used to assess categorical variables. The continuous variables normally distributed were assessed by the student's *t*-test. The Fisher's exact or the chi-square test was adopted for categorical data, and statistical significance was set at *p* < 0.05. The main analysis was performed using generalized estimating equations (GEE) model. The GEE solved the problem of correlation of longitudinal data, utilizing the results of each measurement in the longitudinal data, which greatly reduces the loss of information (20). To clarify whether socioeconomic status affects the effectiveness of ILSM, we conducted several subgroup analyses for physiological health outcomes and health behaviors, and added the interaction terms to generalized estimating equations model to assess the interactions between time (at baseline, 3-month, 6-month, and 18-month) and group (intervention and control). We also used GEE to analyze the health benefits of intervention and control groups among participants with different socioeconomic status. Significance level of the associations in the final model was set at *P*-value 0.05. The data were analyzed using SPSS 20.0 (IBM Corporation, Armonk, NY, USA).

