Our study introduces artificial intelligence driven therapeutic lifestyle changes (AI-TLC) intervention. The study aims to examine the effect of AI-TLC intervention on health behavior and health for obesity pregnant women. Several strengths warrant mentioning. Firstly, this study not only focuses on the treatment of obese individuals, but also considers obesity as a part of a pregnant women network and adopts multi-dimensional lifestyle modification as an intervention. This comprehensive intervention strategy is innovative in the management of obesity pregnant women. Secondly, an interdisciplinary team consisting of physicians, health managers, nutritionists, and artificial intelligence simulated health managers will be formed to provide comprehensive health management programs for obesity pregnant women. Thirdly, this study will introduce AI technology for health intervention to explore the application potential and effectiveness of AI intervention in obesity pregnant women management, which is prospective and innovative. Fourth, this study will conduct short-, medium- and long-term tracking and evaluation of the AI-TLC intervention effects, which will help to comprehensively understand the long-term impacts of the AI-TLC interventions and provide a basis for the development of sustained and effective health management strategies. Fifth, this study will evaluate the economic benefits of different interventions from a cost-benefit perspective and help to provide policymakers and healthcare providers with cost-effective intervention options.

Here are some extended comparisons with similar studies. The efficacy of AI-TLC interventions can be further contextualized by contrasting it with other obesity management strategies. Recent systematic reviews highlight that AI-driven interventions excel in providing real-time personalized feedback, a feature critical for sustaining behavioral changes in high-risk populations (32). For example, hybrid interventions combining digital tools and human support have shown superior long-term weight maintenance compared to purely automated systems, supporting our finding that the AI+Manual group achieved the highest clinical impact (33). This aligns with broader evidence that technology-enhanced programs improve accessibility in resource-limited settings (34), a key consideration for China's maternal healthcare system.

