Next are the differences with the existing literature. Notably, our cost-benefit analysis revealed that the AI-only intervention offered a scalable solution with moderate efficacy, whereas the combined AI+Manual group achieved the highest clinical impact. This contrasts with Perdomo et al., who emphasized surgical and pharmacological interventions as primary strategies for severe obesity (15). However, our results align with Sallam et al., where TLC combined with medication synergistically improved metabolic outcomes (20). Such parallels suggest that hybrid models (AI + human expertise) may bridge the gap between resource-intensive and purely automated interventions.

However, this study has the following limitations. First, despite the high coverage rate of smartphones in China, some patients may not be able to use them well, which may hinder the implementation and reduce the effectiveness of AI interventions. Second, for the collection of the primary and secondary outcomes, we primarily used questionnaire indicators, which may inevitably lead to recall bias. Third, due to the lack of balanced stratification, comparative analyses between subgroups may not be suitable if the sample size of each group is insufficient across groups (e.g., compare the differences and potential influencing factors of AI-TLC intervention effects in different age groups). Fourth, the short-term follow-up period (up to 3 months postpartum) precludes conclusions about long-term weight maintenance. Meta-analyses of lifestyle interventions for obese pregnant women indicate that postpartum weight retention remains a challenge beyond 12 months (35), emphasizing the need for extended follow-up in future studies. Additionally, socioeconomic disparities in AI accessibility—particularly among older or rural populations—may limit generalizability, necessitating stratified analyses in broader cohorts.

Despite these limitations, this study may provide a scientific basis for developing personalized and effective interventions to further improve the health behavior and health of obesity pregnant women. It is expected to provide a new perspective and effective approach to the management of obesity pregnant women.

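### The only listed postpartum visit is given two times that do not overlap, and neither the GEE time points nor the long-term objective fits the stated follow-up

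*Protocol article*

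**What the plan says.** **Visit schedule (section 2.1).** Baseline is placed at about week 12 of pregnancy. For the later assessments the section states: "Follow-up visits are scheduled at approximately 20, 28, and 36 weeks of gestation". The last visit is then dated "as well as at 3 months postpartum (24–32 weeks post-delivery". That makes five assessments, one of them after delivery.

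**Measurement table (section 2.5, Table 1).** The table, titled "Variables and measures collected at evaluation time points", has six columns, T-0 to T-5. Weight and BMI are ticked in all six. No gestational or postpartum week is attached to any column in the text available.

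**Analysis (section 2.6).** The main analysis is a GEE model, with terms for "interactions between time (at baseline, 3-month, 6-month, and 18-month) and group (intervention and control".

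**Long-term aims.** Sub-question 3 in the Introduction asks: "What are the short-term, medium-term, and long-term effects of this intervention program". Section 2.4.1 assigns GEE or Cox models to short-, medium- and long-term impacts. The Discussion lists as a strength that "this study will conduct short-, medium- and long-term tracking and evaluation of the AI-TLC intervention effects".

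**Limitation (Discussion).** The same Discussion states that "the short-term follow-up period (up to 3 months postpartum) precludes conclusions about long-term weight maintenance".

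**The concern.** A visit window should contain its target. Here the target lies outside the window, so anyone following section 2.1 has two incompatible instructions for the same visit. Weight and BMI are primary outcomes under section 2.4.1, and this is the only postpartum assessment the schedule lists. A group difference at about 3 months after birth and one at about 5.5–7.4 months are different estimands, and the text does not fix which one the trial will report.

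Two further statements depend on this date and also disagree with it. The GEE time factor names times that the schedule does not contain. The long-term objective is promised in three places and, for weight maintenance, ruled out in a fourth. What is at stake is the meaning of the postpartum estimate and how far the conclusions may reach in time.

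**Working it through.** No sample-size formula applies. The check is a calendar conversion and a comparison of the places that give times.

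**Inputs.** Baseline at 12 weeks of gestation; follow-up at 20, 28 and 36 weeks; last visit at 3 months postpartum, or 24–32 weeks post-delivery (all section 2.1). Model times: baseline, 3, 6 and 18 months (section 2.6). Assumption, not in the documents: delivery at 37–42 weeks.

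**Step 1: conversion.** Weeks per month = 365.25 / 12 / 7 = 4.348.
- 3 months = 3 × 4.348 = 13.0 weeks.
- 24 weeks = 24 / 4.348 = 5.5 months; 32 weeks = 32 / 4.348 = 7.4 months.
- Distance from target to window: 24 − 13.0 = 11.0 weeks to its opening, 32 − 13.0 = 19.0 weeks to its close.

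The plan's equation of 3 months with 24–32 weeks is therefore not reproduced. Reading 3 months loosely as 2.5–3.5 months gives 10.9–15.2 weeks, which still does not reach 24.

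**Step 2: could the window run from baseline instead of delivery?** Three months postpartum, counted from baseline, is (37 − 12) + 13.0 = 38.0 weeks to (42 − 12) + 13.0 = 43.0 weeks. That also lies outside 24–32 weeks, so a change of origin does not rescue the sentence.

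**Step 3: both versions on the model's time scale (months from baseline).**

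| Time point | Earliest (delivery at 37 weeks) | Latest (delivery at 42 weeks) |
|---|---|---|
| 3 months postpartum | 38.0 / 4.348 = 8.7 | 43.0 / 4.348 = 9.9 |
| 24–32 weeks post-delivery | (25 + 24) / 4.348 = 11.3 | (30 + 32) / 4.348 = 14.3 |

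**Step 4: the section 2.6 times on the visit calendar, counted from baseline.**
- 3 months: 12 + 13.0 = 25.0 weeks of gestation, between the 20- and 28-week visits.
- 6 months: 12 + 26.1 = 38.1 weeks of gestation, after the 36-week visit.
- 18 months: 12 + 78.3 = 90.3 weeks, which is 90.3 − 42 = 48.3 to 90.3 − 37 = 53.3 weeks after delivery.

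The 18-month point is later than 13 weeks and later than 32 weeks after delivery, so it lies beyond either version of the last visit. Counting from delivery does not help: 18 months is then 78.3 weeks postpartum.

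**Step 5: number of time points.** Section 2.1: 1 + 3 + 1 = 5. Table 1: T-0 to T-5 = 6. Section 2.6: 4.

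**The case against.** The best defence is that the bracket is a single drafting slip. The main words of section 2.1 and the limitations paragraph both say 3 months postpartum, and only the parenthesis departs from them. That does show which way the text leans. It does not settle the matter, because section 2.1 is the operative schedule and still carries the other window, while the supporting statement is a remark in the Discussion. Nor does it explain the 18-month time in section 2.6.

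On long-term effects, the authors disclose the limitation, it concerns weight maintenance specifically, and the term long-term is never defined. This narrows the conflict but does not remove it: weight is a primary outcome, and the strength and the limitation stand in the same Discussion.

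Some stronger readings are tempting and are not supported:

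- *T-5 is a surplus column.* A reader might infer this from six columns against five visits. But section 2.2 describes a pre-enrolment assessment with questionnaires and examinations, which could be the sixth. So could a delivery assessment, and Figure 1, which is not shown, may define the labels. If the columns run in time order, T-5 is probably the postpartum visit itself. The count alone shows only that labels are needed.
- *Visit timing would differ by arm and bias the comparison.* The documents give one schedule for all participants, and nothing in them indicates that arms would be seen at different times.
- *The gap can be expressed in kilograms.* The documents give no rate of postpartum weight change. Under a common schedule, a shift in mean weight would in any case not by itself bias the contrast between arms.
- *No outcome has a fixed time.* The visits at 20, 28 and 36 weeks are clearly dated.

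**Conclusion.** The point holds as an internal contradiction in the schedule. The two times given for the postpartum visit are 11 to 19 weeks apart and cannot both be right; this needs no assumption beyond the calendar. The GEE time points do not match the scheduled visits, and the 18-month point lies beyond either version of the last visit. Placing it at about 48–53 weeks after delivery assumes that months run from the 12-week baseline and that delivery is at 37–42 weeks. The long-term promise in Sub-question 3, section 2.4.1 and the strengths is wider than the stated follow-up allows, at least for weight maintenance.

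The defect is confined to the postpartum estimate, the model's time factor and the long-term claims. It does not touch the assessments in pregnancy. The mismatch in the number of time points is weaker, supporting evidence: it calls for labels and does not prove an undated or redundant visit. The contradiction should still be corrected, because an unseen analysis plan cannot make the two stated times agree.

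**What to change.** 1. Reconcile section 2.1, section 2.6 and the limitations paragraph to one postpartum assessment time, with a window that contains its target and is the same in all three arms.
2. Set the time factor of the GEE model to the visits actually scheduled, and state the origin from which time is counted.
3. Label T-0 to T-5 in Table 1 with those visits, and say what the sixth column is (for example the pre-enrolment or a delivery assessment). Do not remove T-5 on the assumption that it is spare.
4. Restrict Sub-question 3, the long-term analysis in section 2.4.1 and the corresponding strength in the Discussion to effects up to the last scheduled visit.

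The cost is edits to wording and one table, and a narrower long-term claim. No extra visits are required.

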**Figure 1 F1:**
[figure not shown]
Flowchart of randomized controlled trial.

#### 2.1.1 Sample size

As this study is a randomized controlled trial, the respondents will be divided into manual intervention group, artificial intelligence (AI) intervention group, artificial intelligence and manual combined intervention group, and observe the BMI of pregnant women, maternal weight and maternal adverse pregnancy outcomes as the main outcome indicators. The sample size was calculated based on an expected effect size of 0.5, which corresponds to the minimal clinically important difference (MCID) of the primary outcome. This MCID was determined based on previous literature and clinical judgment. Setting bilateral α = 0.05, the degree of certainty was 90%. Using the PASS15 software, we obtained a sample size of N1 = 40 cases for the group and N2 = 40 cases for the group and N3 = 40 cases for the group. For a total of at least 120 subjects to be included in the study.

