## 1 Introduction

Obesity is an abnormal or excessive fat accumulation that can impair health. A research study shows that the total number of obese children, adolescents and adults worldwide by 2022 has exceeded 1 billion, of which 879 million are adults. Since 1990, obesity rates among adults have more than doubled among women (1). In China, the problem of overweight and obesity among residents is increasingly prominent, and the rate of overweight and obesity among all age groups in urban and rural residents continues to rise, and more than half of adult residents are overweight or obese. Obesity is not only an independent health problem, but also an important risk factor for multiple chronic diseases such as type 2 diabetes, cardiovascular disease, hypertension, and so on (1, 2). Obesity often coexists with other chronic diseases, creating a complex network that complicates treatment and management. Furthermore, obesity is linked to several biological mechanisms, such as inflammation, oxidative stress, and endocrine disorders, which may collectively contribute to the development of chronic diseases (3). With the increasing rate of obesity worldwide, the incidence of chronic diseases increases, placing a substantial burden on individual health, healthcare systems and socioeconomic (4).

Maternal obesity is associated with a range of adverse pregnancy outcomes, including gestational diabetes mellitus, gestational hypertension, preeclampsia, need for cesarean delivery, and large for gestational age (5–8). These complications not only affect the health of the mother during pregnancy but may also have long-term consequences for the child, such as increased risk of prematurity, large for gestational age, birth-related trauma, hypoglycaemia, neonatal intensive care unit admission, stillbirth, increased risk of obesity and metabolic disorders in later life (8–11).

According to the study, obese patients had 46% more hospitalization, 27% more clinic and outpatient costs and 80% more prescription drugs compared with normal weight individuals (12). In recent years, several guidelines and expert consensus on obesity and chronic diseases have been published at home and abroad, but most of them are suggestions for evaluation methods or diagnosis and treatment procedures, and lack systematic prevention and management countermeasures. Therefore, it is important to study effective strategies for chronic obesity intervention to improve public health.

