### 2.4 Outcomes

#### 2.4.1 Primary outcomes

The primary outcomes of the study include maternal body mass index (BMI), maternal weight, and adverse pregnancy outcomes. The primary outcome measures (such as BMI, maternal weight, and adverse pregnancy outcomes) will be assessed using Repeated Measures ANOVA or Mixed Effects Models to evaluate the intervention effects. For long-term effect analysis, Generalized Estimating Equations (GEE) or Cox Proportional Hazards Models will be employed to assess the short-term, medium-term, and long-term impacts of the interventions. Cost-effectiveness analysis will be conducted using Quality-Adjusted Life Years (QALY) and Incremental Cost-Effectiveness Ratios (ICER) to evaluate the economic efficiency of different intervention measures, with sensitivity analysis performed to verify the robustness of the results.

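### The single sample-size calculation does not say which of three main outcomes it serves; if it is read as covering adverse pregnancy outcomes, 40 per arm does not deliver the stated 90%

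*Protocol article*

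**What the plan says.** Section 2.1.1 names three main outcomes together: the trial will "observe the BMI of pregnant women, maternal weight and maternal adverse pregnancy outcomes as the main outcome indicators". The next sentences give one calculation. It uses an "expected effect size of 0.5, which corresponds to the minimal clinically important difference (MCID) of the primary outcome", in the singular, with no unit, standard deviation or event rate. The error rates are given as "Setting bilateral α = 0.05, the degree of certainty was 90" per cent, which I read as two-sided 0.05 and 90% power. The result is "N1 = 40 cases for the group and N2 = 40 cases for the group and N3 = 40 cases for the group", and then "For a total of at least 120 subjects to be included in the study".

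Section 2.4.1 confirms the status of all three: "The primary outcomes of the study include maternal body mass index (BMI), maternal weight, and adverse pregnancy outcomes". It does not define the adverse-outcome endpoint further. The Introduction gives examples of what the term means in this population: "adverse pregnancy outcomes, including gestational diabetes mellitus, gestational hypertension, preeclampsia, need for cesarean delivery, and large for gestational age". The article gives no event rate, risk difference or separate calculation for adverse outcomes. Section 2.6 names Fisher's exact test or the chi-square test for categorical data.

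**The concern.** One calculation follows directly on a list of three main outcomes, and nothing limits it to any of them. A reader can easily carry the 90% across to all three. An effect size of 0.5 with no unit is most naturally a difference in means in standard-deviation units. That can describe weight or BMI, but it is not a minimal important difference for an event.

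What is at stake is how the adverse-outcome result is read. Placed beside a stated 90%, a non-significant comparison may be taken as good evidence of no difference when the interval around it is wide. A claim that adverse outcomes were reduced, such as the one already in the article's Discussion, would also need more information than 40 women per arm usually supply.

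**Working it through.** **Inputs from the article (section 2.1.1).** n = 40 per arm, two-sided α = 0.05, 90% power, effect size 0.5.

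**Assumptions.** 40 women analysed per arm, two arms compared at a time, and no adjustment for multiple comparisons. The adverse outcome is treated as yes/no, following the Introduction's examples. Comparator risk is varied from 20% to 60% because the article gives none.

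**Step 1. The plan's own figure, read as a 0.5 SD difference in means.**

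n per arm = 2 × [(1.960 + 1.282) / 0.5]² = 84.1, so 85 (86 by the t-test). The stated 40 is not reproduced.

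Power with 40 per arm = Φ(0.5 × √(40/2) − 1.960) = Φ(0.276) = 61% (60% by the t-test).

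Difference detectable at 90% = (1.960 + 1.282) × √(2/40) = 0.72 SD (0.73 by the t-test).

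Other common readings also miss 40 per arm: one-sided 0.05 gives 69, 80% power gives 63, and three-group ANOVA with f = 0.5 gives about 54 in total. Unstated repeated-measures assumptions can come close. For example, the mean of four visits with a within-woman correlation of 0.3 gives 40.

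**Step 2. The same 40 per arm applied to a yes/no outcome.**

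Power = Φ{ [ |p1 − p2| × √40 − 1.960 × √(2p̄(1 − p̄)) ] / √(p1(1 − p1) + p2(1 − p2)) }, where p̄ is the mean of p1 and p2.

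Example, 50% to 16.7%: (2.106 − 1.307) / 0.624 = 1.281, and Φ(1.281) = 90%.

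Example, 50% to 25%: (1.581 − 1.342) / 0.661 = 0.362, and Φ(0.362) = 64%.

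| Assumed comparator risk | Risk needed in the other arm for 90% power | Power if the risk is halved |
|---|---|---|
| 60% | 25% | not tabulated |
| 50% | 16.7% | 64% |
| 40% | 9.5% | 50% |
| 30% | 3.6% | 36% |
| 20% | not attainable (a fall to zero gives about 86%) | 24% |

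These figures are on the lenient side. At 50% versus 17% the formula gives 89.4%, Fisher's exact test gives 84.6%, and testing at 0.05/3 for three pairwise comparisons gives 78.3%.

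**Step 3. Reading 0.5 as an effect size for proportions (Cohen's h).**

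h = 2·arcsin√p1 − 2·arcsin√p2 = 0.5 corresponds to 50% to 26%, or 40% to 18%. Power with 40 per arm is about 60% in both cases, and 90% needs 85 per arm.

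**Step 4. Precision.**

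The 95% half-width for a risk difference is 1.96 × √(2p(1 − p)/40), which is 0.20 at p = 0.30 and 0.22 at p = 0.50. That is about ±20 to 22 percentage points.

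**The case against.** Five points can fairly be made against this.

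- **The plan makes no explicit power claim for adverse outcomes.** Section 2.1.1 ties the 0.5 to a single primary outcome, and sizing a trial on one of several outcomes is common practice. This stands. A reader might infer that the plan claims 90% power for adverse outcomes, but the text does not say so. The fault is that it does not say which outcome is meant.
- **The standardised and yes/no readings are interpretations.** The article does not call the 0.5 standardised. The list of events comes from background text and does not define the endpoint; a composite, separate events and a count would each behave differently. This also stands, and the result is therefore conditional. If 0.5 meant raw BMI units, it would still say nothing about events.
- **Every event figure rests on an assumed risk.** That is true, which is why a range is shown. The conclusion is the same across it.
- **This overlaps with the general shortfall.** In part it does. Under Cohen's h the power and required n match those for a 0.5 SD mean difference. What remains separate is that raising the arms to 85, or correcting the power for weight, would still not give a basis for the event outcome.
- **The consequences can be overstated.** A reader might infer that an unsafe arm could pass as safe, but the article states no safety or non-inferiority rule for it to pass. A reader might also infer that any large reduction would usually be missed. Halving a 50% risk has 64% power, so that is not so at higher risks.

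**Conclusion.** The point holds as one about the scope of the sample-size statement. The article lists three main outcomes, gives one calculation and does not assign it to any of them. Read as applying to adverse pregnancy outcomes, the 90% is reached only for very large falls in risk and is out of reach from a comparator risk of 20%. An effect of 0.5 on the proportion scale has about 60% power. The 90% does not hold for weight or BMI either on the plain two-group reading, so it should not simply be moved to one of those outcomes. All event figures assume 40 analysed per arm, pairwise tests at two-sided 0.05, a yes/no endpoint and the comparator risks shown.

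**What to change.** In section 2.1.1:

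- Name the single continuous outcome, weight or BMI, that the calculation concerns.
- Restate its power without carrying over the 90%. With 40 per arm this is about 60% for 0.5 SD, or a detectable difference of about 0.73 SD at 90%. If the calculation used repeated measures, state those assumptions.
- State that the calculation does not cover adverse pregnancy outcomes, and add the event difference that 40 per arm can detect over a stated range of comparator risks.

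In section 2.4.1, report adverse pregnancy outcomes as counts and risk differences with 95% confidence intervals, label them as not powered, and say that a non-significant result will not be read as no difference.

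The cost is wording only, with no added patients. The drawback is that the stated power becomes less favourable.

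### The inputs printed in the sample size section do not give 40 women per arm; read as a pairwise difference of 0.5 SD, 40 per arm has about 60% power, not 90%

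*Protocol article*

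**What the plan says.** Protocol article, section 2.1.1, gives these inputs and this result:

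- Effect: the "sample size was calculated based on an expected effect size of 0.5". The section treats this value as the MCID for its primary endpoint.
- Error rates: "Setting bilateral α = 0.05", and "the degree of certainty was 90" (a percentage), which I take to mean power.
- Result, from PASS15: "we obtained a sample size of N1 = 40 cases for the group and N2 = 40 cases for the group and N3 = 40 cases", that is, 40 in each of the three arms. The total follows: "For a total of at least 120 subjects to be included in the study".

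The same section names three main outcomes: "observe the BMI of pregnant women, maternal weight and maternal adverse pregnancy outcomes as the main outcome indicators". It does not say which of them the 0.5 belongs to. Nor does it give the test, the effect-size metric, an SD, a within-woman correlation, a multiplicity adjustment or an allowance for loss.

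Section 2.4.1 says the primary outcomes "will be assessed using Repeated Measures ANOVA or Mixed Effects Models to evaluate the intervention effects". Section 2.6 names GEE as the main analysis. Neither method appears as an input to the sample size calculation.

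**The concern.** An effect size of 0.5 that is called a minimal important difference is most naturally a standardised mean difference between two arms. At two-sided 5% and 90% power it needs roughly twice the planned number per arm.

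The power figure affects how the results will be read. All three arms receive an active lifestyle programme, and the second sub-question in the introduction is which level of intervention is best value. A non-significant AI-versus-manual comparison could then be taken as showing no difference, with cost deciding between the arms. A stated 90% power for the MCID supports that reading; 60% would not.

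**Working it through.** **Inputs from section 2.1.1:** effect size 0.5, two-sided alpha 0.05, power 0.90, n = 40 per arm, three arms.

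**1. Two arms, d = 0.5 (most natural reading).**
- Normal approximation: n per arm = 2(1.960 + 1.282)²/0.5² = 2 × 10.51/0.25 = 84.1, so 85.
- Exact noncentral t: n = 85.03, so 86 per arm (85 gives 89.99%, 86 gives 90.3%).
- Power at 40 per arm, normal approximation: Φ(0.5 × √(40/2) − 1.960) = Φ(0.276) = 60.9%. Exact t: 59.8%.
- Detectable difference at 40 per arm (exact t): 0.73 SD with 90% power, 0.63 SD with 80%.

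**2. One-way ANOVA, three arms, noncentral F, noncentrality = N f².**

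| Meaning given to 0.5 | f | n per arm for 90% | Power at 40 per arm |
|---|---|---|---|
| Cohen's f | 0.50 | 18 | 99.9% |
| 0.5 SD step between adjacent arms | 0.41 | 27 | 98% |
| Largest gap 0.5 SD, two arms equal | 0.236 | 77 | 62% |
| Largest gap 0.5 SD, third arm midway | 0.204 | 103 | 49% |

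With 40 per arm, 90% power corresponds to f of about 0.33, which is not stated.

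**3. Other settings of the two-arm test (normal approximation, n per arm).** One-sided 90%: 69. Two-sided 80%: 63. One-sided 80%: 50. Bonferroni over three comparisons at 90%: 109. A paired t test needs 44 pairs, but that is a within-woman comparison, not a comparison of arms. None gives 40.

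**4. What does come near 40.** Here 0.5 is in SDs of a single raw measurement, and the correlations are my assumptions.
- One follow-up adjusted for baseline: the variance is multiplied by 1 − r². With r = 0.73, 86 × (1 − 0.533) = 40.2; power at 40 is about 90%.
- Mean of m = 4 follow-ups, not baseline-adjusted, equal correlation ρ: variance factor (1 + 3ρ)/4. With ρ = 0.3 it is 0.475; power at 40 is 90% by the normal approximation and 89% by the t test. With ρ = 0.5 it is 0.625 and power is about 80%.
- Mean of four follow-ups, baseline-adjusted: variance factor (1 + 3ρ)/4 − ρ². It is largest at ρ = 0.375, where it is 0.391; power at 40 is then 94%, so at least 94% for any ρ. With three follow-ups the minimum is about 91%. Both figures assume equal correlations among all visits and a constant effect from the first follow-up on.

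**5. Loss and multiplicity on the d = 0.5 reading (exact t).** An assumed 10% to 20% loss leaves 36 to 32 per arm and 55% to 50% power. With no loss, power is 48% at alpha 0.025 and 42% at 0.05/3.

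**The case against.** The strongest reply is that the article never says 0.5 is a pairwise d. If it were Cohen's f, or a step of 0.5 SD between adjacent arms, 40 per arm would be more than enough, so the text does not settle even the direction of the error. This stands as a limit on the 60% figure. It does not rescue the 40, because those readings give 18 and 27 per arm. Cohen's f = 0.5 also puts the arms more than 1 SD apart, which fits poorly with a minimal important difference.

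The second reply is that the planned analyses are longitudinal, that section 2.1 schedules a baseline and four follow-ups, and that a repeated-measures calculation is therefore a standard choice. This also stands. A reader might infer that the figures cannot be reconciled under any standard method; step 4 shows that they can, given a suitable correlation. What the article lacks is any statement that such a calculation was made, or with which correlation.

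A reader might also infer that 90% power requires a baseline to follow-up correlation of at least 0.73. That holds only for a single baseline-adjusted follow-up, and is not a general condition.

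Finally, a journal article condenses the full protocol, which may hold the test and the correlation. But the article prints a set of inputs and presents 40 per arm as their result, and by the tests that those inputs would ordinarily imply, it is not.

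**Conclusion.** The point holds as a failure of the printed inputs to reproduce the printed sample size. By a two-group t test or a one-way three-arm ANOVA, no reading of 0.5 examined here gives 40 per arm. Read as a pairwise difference of 0.5 SD at one time point, without baseline adjustment, loss or multiplicity correction, power is about 60% against the stated 90%, and 86 per arm would be needed against 40. The chance of missing a true 0.5 SD difference would then be about 40% rather than 10%.

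A reader might go further and infer that the trial is underpowered whatever the analysis. The article does not support that. The metric is not named, and under the idealised assumptions of step 4 a baseline-adjusted analysis of several follow-ups could exceed 90% power with 40 per arm. An effect that builds up over pregnancy would lower those figures. The calculation needs correcting because the trial relies on a power figure that cannot be traced to its inputs, and restating it is cheap.

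**What to change.** In section 2.1.1:

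1. Name the outcome to which 0.5 refers, the effect-size metric and the test.
2. If 0.5 is a pairwise standardised difference at one time point, state that 40 women per arm give about 60% power at two-sided 5%, and that the detectable difference is 0.73 SD with 90% power (0.63 SD with 80%).
3. Keep the 90% claim only if it is recomputed for the repeated-measures or baseline-adjusted analysis actually planned. State the number of follow-ups, the correlation and its source, and the assumed pattern of the effect over time. Settle the number of follow-ups first: section 2.1 schedules four, while Table 1 has five columns after T-0.
4. Adjust the BMI and weight comparisons for the T-0 value, which Table 1 already collects. This does not carry over to adverse pregnancy outcomes, which have no baseline value; if they remain primary, their power needs its own statement.
5. Do not write in a general correlation threshold of 0.73.

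No extra patients or data are needed. The cost is a revised paragraph and, on the likelier reading, a less favourable stated power.
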